### Data security, access, and back-up

All data will be stored on the Lausanne University Hospital’s secure server. Study data entered into the eCRF are only accessible by authorized persons. Password protection and user right management ensure that only authorized study personal and local authorities (if necessary) will have access to the data during and after the study. Biological material is appropriately stored in a restricted area only accessible to authorized personnel according to the regulation of the urology biobank of Lausanne University Hospital (identification with badge).

### Sample size calculations

The literature review showed a postoperative infectious rate between 25 and 45% among patients treated with cystectomy [4, 5]. Prior clinical data from cystectomy patients at CHUV resulted in an infectious rate at 30 days after surgery of 30%. As showed before, the literature review showed an infection between 25 and 45% among patients treated with cystectomy. Assuming a normal distribution for infectious complications after cystectomy and a common standard deviation in both study arms, desired probabilities of type I error (*α*) of 5% and of type II error (*β*) of 20% (i.e., 80% statistical power) and applying a two-sided test, 110 informative patients per arm (i.e., a total of 220) would be needed to decrease the rate of infectious complications by 17% in the IN group (37% infections at 30 days after surgery in the control group vs 20% in the IN group). Since we anticipate a possible dropout rate of up to 5%, a total of 232 patients are intended for enrolment in the study (116 patients per group). To achieve adequate participant enrolment, three Swiss hospitals participate to this study: University Hospital of Lausanne, University Hospital of Bern, and Hospital of Riviera-Chablais, with an estimated rate of recruitment of 50, 25, and 10 patients per year, respectively.

### Statistical analysis

Ordinal and continuous data will be presented by study group in the form of descriptive statistics, as number of patients, mean, standard deviation, minimum, median, and maximum. Categorical data will be presented by study group using contingency tables with absolute and relative frequencies.

Complications rate will be presented using contingency tables with absolute and relative frequencies, overall and then by study group. The complication rate will be compared between groups using a Chi2 test. Mortality after surgery and postoperative complication-free survival will be analyzed using Kaplan–Meier curves. The study groups will be compared with a log-rank test. Nutritional status will be documented, and subgroup analysis of well-nourished patients randomized to the IN group will be undertaken at the end of the study. No imputations will be done on missing data. So, for longitudinal analysis mixed method analysis will be performed. Non-compliant patients from both arms will be maintained in the study, with no exclusion from the primary intention-to-treat analysis, however withdrawn from the per-protocol analysis. There is no data monitoring committee, owing to very good and well-known safety profiles of the IN and to the short follow-up period.

Other subgroup analyses will be performed (1) to test the effect of neoadjuvant chemotherapy and the risk of malnutrition on the primary outcomes and (2) to test the impact of the ERAS® compliance on the primary and secondary outcomes.

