## Methods

### Study design

The present study (approval #2022–01528 version 5) is designed as a multicenter, prospective, controlled, pragmatic, superiority, parallel-group comparative clinical trial with block randomization stratified by centers (Fig. 1 and Table 1). Patients will be randomly assigned to 2 groups (per center randomization): intervention group (7 days of preoperative oral supplementation with an immune-enhanced oral nutrition (Oral Impact®, Nestlé Nutrition, Switzerland)) or control group (standard of care, no preoperative IN). During an overall study duration of 4 years, a total of 232 patients (116 in each arm) will be included (Table 2
). Allocation consignment will be generated by a dedicated research nurse at each center, through centralized block randomization via the Interface Web Response System (IWRS) developed within the electronic case report form (eCRF). Equilibrated randomization will be performed on a site-stratified basis to avoid imbalanced randomization between clinical sites where patient recruitment may differ. The allocation sequence is concealed from the investigators enrolling and assessing the patients.

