### Clinical outcomes

The primary endpoint is to investigate the infectious complications rate at 30 days after surgery. All type of infectious complication will be considered and graded according to the Clavien’s grade.

Secondary clinical outcome is Comprehensive Complication Index (CCI) evaluated at 30 and 90 days after surgery. Postoperative complications will be graded according to their severity. A validated therapy-oriented, modified Clavien-Dindo classification will be used to asses complication grade [15]: major complications are defined as grade 3–4; grade 5 corresponds to mortality.

Mortality rate at 30 and 90 days after surgery, postoperative complication-free survival, treatment compliance, impact of IN on oncologic and non-oncologic patients, role of IN in patients undergoing neoadjuvant chemotherapy, and quality of life after surgery will also be investigated.

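### Randomisation is stratified by centre, but the named Chi2 and log-rank tests ignore centre: valid, slightly conservative, and improvable at no cost

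*Protocol article*

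**What the plan says.** The Study design section describes a "parallel-group comparative clinical trial with block randomization stratified by centers" and gives the purpose: "Equilibrated randomization will be performed on a site-stratified basis to avoid imbalanced randomization between clinical sites where patient recruitment may differ". Under Clinical outcomes, "The primary endpoint is to investigate the infectious complications rate at 30 days after surgery".

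The Statistical analysis section names one test for proportions: "The complication rate will be compared between groups using a Chi2 test". For mortality and complication-free survival, after Kaplan-Meier curves, it says: "The study groups will be compared with a log-rank test". Neither sentence mentions centre, strata or a centre term. The mixed-model sentence in that section concerns longitudinal data and does not reach the 30-day endpoint.

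The Sample size calculations section works with 37% infections in the control arm against 20% with immunonutrition, at "type I error (*α*) of 5% and of type II error (*β*) of 20% (i.e., 80% statistical power"), and concludes that, "applying a two-sided test, 110 informative patients per arm (i.e., a total of 220) would be needed". It plans 232 patients to allow for 5% dropout and expects 50, 25 and 10 patients per year from Lausanne, Bern and Riviera-Chablais.

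**The concern.** Stratified randomisation balances the arms within each centre. Differences between centres then cannot contribute to the chance difference between arms. A plain Chi2 test does not know this: it takes its variance from the pooled infection rate, which includes the variation between centres. If the centres have different infection risks, the test uses a variance that is too large, rejects less often than 5% under the null, and loses some power under the alternative. The same reasoning applies in direction to an unstratified log-rank test.

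At stake is a little of the power that the design pays for. The plan has almost none to spare: 110 per arm gives 80.2%.

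**Working it through.** **1. The plan's own figure.** Two proportions, p1 = 0.37, p2 = 0.20, mean 0.285, two-sided 5%, 80% power, pooled variance under the null, no continuity correction:

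n = [1.960·√(2·0.285·0.715) + 0.842·√(0.37·0.63 + 0.20·0.80)]² / 0.17²
= (1.2512 + 0.5277)² / 0.0289 = 109.5, so 110 per arm.

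Dropout: 220 / 0.95 = 231.6, so 232. Both stated figures reproduce with an unstratified formula, so centre plays no part in the sample size either.

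**2. Centre mix.** From 50:25:10 per year, the shares are 59%, 29% and 12%. With 110 per arm this is 65, 32 and 13 patients.

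**3. Size of the conservatism, by formula.** Let p_k be the infection rate in centre k, w_k its share and p̄ the overall rate. The plain test uses p̄(1−p̄). Under stratified randomisation the relevant variance is Σ w_k p_k(1−p_k), which equals p̄(1−p̄)·(1−s), where s = Σ w_k(p_k−p̄)² / [p̄(1−p̄)] is the between-centre share. The actual two-sided error is about 2·[1−Φ(1.960/√(1−s))]. All spreads below are assumptions, scaled to an overall control rate of 37%:

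| Control rates, Lausanne/Bern/Riviera-Chablais | s | 1.960/√(1−s) | Approximate type I error |
|---|---|---|---|
| 37/37/37% | 0 | 1.960 | 5.0% |
| 30/45/52% | 0.032 | 1.992 | 4.6% |
| 28/49/49% | 0.046 | 2.006 | 4.5% |
| 25/60/40% | 0.104 | 2.070 | 3.8% |

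**4. Simulation.** 400,000 trials per scenario, 65/32/13 per arm, marginal rates 37% vs 20%, common odds ratio across centres, uncorrected Chi2 against the centre-stratified Cochran-Mantel-Haenszel (CMH) test. Type I error was simulated with the control rates in both arms.

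| Control rates | Type I error, Chi2 vs CMH | Power, Chi2 vs CMH | Gain in points |
|---|---|---|---|
| 37/37/37% | 5.0% vs 4.9% | 80.2% vs 80.4% | 0.1 |
| 30/45/52% | 4.6% vs 5.0% | 80.7% vs 81.6% | 0.9 |
| 28/49/49% | 4.5% vs 5.0% | 80.9% vs 82.2% | 1.3 |
| 25/60/40% (wide) | 3.9% vs 5.0% | 81.5% vs 84.2% | 2.7 |

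Gains are taken before rounding. The simulated Chi2 errors agree with the formula in step 3.

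**5. A different convention gives the same gap.** Fix the odds ratio within each centre at (0.20/0.80)/(0.37/0.63) = 0.426 and take control rates of 30/47/47%. With all 232 patients, power is 80.9% vs 81.7%; with 110 per arm it is 78.6% vs 79.5%. The levels differ from step 4 partly because a within-centre odds ratio of 0.426 gives an overall immunonutrition rate of about 20.4% rather than 20%. The gain is again 0.8 to 0.9 point.

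**6. Log-rank.** The article gives no mortality rate, no complication-free survival rate and no hazard ratio, so no loss can be computed.

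**The case against.** The strongest reply is that nothing is wrong. The plain Chi2 test keeps its error at or below 5%, it matches the formula behind the 110 per arm, and the gain from stratifying is about one point. All of this stands, and it limits the point to a minor improvement.

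A second reply is that the centres may hardly differ. The article prescribes the same antibiotic prophylaxis, the same ERAS-based perioperative protocol and a standardised surgical technique in all three. A reader might infer that the article's own figures show centre differences: if Lausanne stays at 30%, the other two centres must average (0.37 − 0.588×0.30)/0.412 = 47% for the overall control rate to be 37%. The documents do not support that inference. The 30% is one centre's history, 25 to 45% is a range across published series, and 37% is a planning assumption; none of them compares these three centres.

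A reader might also infer that ignoring centre pushes power well below 80%. With assumed control rates of 25/45/45% and 232 patients, Chi2 power is indeed about 77%, but CMH reaches only about 78.4%. That scenario has an overall control rate near 33%, and with 33.3% in every centre Chi2 power is already 79.2%. Only the gap of about 1.3 points is due to the choice of test.

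Finally, a log-rank test named in an article may still be stratified in an analysis plan that is not shown. That is possible, and the log-rank part is correspondingly weaker. For the proportions, the article does commit to a test, and as worded it takes no account of the design's one stratification factor.

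**Conclusion.** The point holds as a minor one. The only tests named ignore the factor by which patients are randomised. The primary comparison stays valid and is slightly conservative if centres differ in infection risk. The cost is about 0.1 point of power with equal centres, about 1 point under a moderate spread, and up to about 3 points under a wide one. These sizes rest on assumed centre rates, the 50:25:10 mix, a common odds ratio and 220 to 232 patients analysed. The direction does not depend on the particular rates chosen.

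Three stronger readings are not supported. The type I error is not inflated. The sample size is not wrong for this reason. Nor does the article promise only a p-value: it announces absolute and relative frequencies by study group, and the interval for the difference is detail that an article may leave to the full protocol or analysis plan. A gain from adjusting also for nutritional risk or neoadjuvant chemotherapy would rest on an explained variance that the documents do not give, so it forms no part of this point.

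**What to change.** In the Statistical analysis section:

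- Make the primary test a Cochran-Mantel-Haenszel test, stratified by centre, of the proportion of patients with an infectious complication within 30 days of surgery.
- Report the matching Mantel-Haenszel risk difference.
- Stratify the log-rank test for mortality and complication-free survival by centre.
- Keep the plain Chi2 and log-rank tests as sensitivity checks.

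This costs one or two sentences, with no extra patients or data, and 232 stands. It should be fixed before outcomes by arm are seen: the Roles and responsibilities section states that the data analyst is not blinded, so a change of test made later would be open to challenge. If the analysis plan already stratifies by centre, it is enough to bring the protocol wording into line.

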## Introduction

Radical cystectomy (RC) with extended bilateral pelvic lymph node dissection (PLND) represents the best available treatment for muscle-invasive BC [1]. Furthermore, this major surgery may be the treatment of choice for non-malignant pathologies, such as interstitial cystitis, painful bladder syndrome, neurogenic bladder, hemorrhagic radiation cystitis, infectious diseases of the bladder, endometriosis, and refractory genitourinary fistulae [2] in patients who have failed previous conservative therapy.

Although cystectomy is considered as an extended major surgery, it has unique features that preclude any outcomes extrapolation from other abdominal surgeries (i.e., colonic resections, gynecologic procedures). These include lymph node resection, longer operative time, significant bleeding, urinary diversion with bowel resulting in metabolic changes, and peritoneal soiling with urine [3].

Despite standardized surgical technique and the development of new perioperative care protocols, cystectomy morbidity remains a serious challenge for urologists. Postoperative complications lead to longer length of stay and worse survival. Infectious complications, including pneumonia, urinary tract infections, surgical site infections, septicemia, and shock, are relatively frequent after cystectomy, rated between 25 and 45% [4, 5]. Patients undergoing cystectomy for a bladder cancer or a benign disease have the similar risk of complications [6]. Antibiotic prophylaxis practices are highly heterogeneous in cystectomy and there is a lack of adherence in guidelines [7].

Careful perioperative risk reduction in patients undergoing major surgery is an evolving key concept to decrease postoperative morbidity rates. Many risk factors, such as repeated radio-chemotherapy regimens, pre-existing co-morbidities, and increased age, can hardly be influenced. Although malnutrition has been identified as an independent risk factor for morbidity and mortality after cystectomy [8–10], there is no recommendation with regard to preoperative screening and/or treatment of malnutrition in guidelines for cystectomy. In most of hospitals where cystectomies are performed, there is no standardized malnutrition screening policy and malnourished patients undergoing surgery are therefore neither identified nor treated.

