Nutritional Risk Status (NRS) Score will be performed in each patient before inclusion. Preoperative carbohydrate loading will be allowed in both groups in case of malnutrition and at discretion of the referent physician. Malnutrition status will not impact the group allocation. This trial will be conducted in accordance with the Good Clinical Practice Guidelines and applicable local regulations. Moreover, we used the SPIRIT reporting guidelines to write the protocol (Supplementary Table 1). The INCyst Trial is supported by the Swiss National Science Foundation (#32003B_207837). The Swiss National Science Foundation is not involved in the design of the study and collection, analysis, and interpretation of data and in writing the manuscript.

**Table 2 Tab2:** Schedule of enrolment, interventions, and assessments

**Study periods**	**Screening**	**Pre-operative**	**Follow-up**				
**Visit**	**V0**	**V1**	**V2**	**V3**	**V4**	**V5**	**V6**
Time (day)	J-30* /-8	J-1/0	J0+1	J0+5	end of hospitalization	J0+30+/-10	J0+90 +/-20
Informed consent	X						
Demographic characteristics	X						
Medical history	X						
In-/Exclusion criteria	X						
Physical examination	X	X	X	X	X	X	X
Weight		X	X	X	X	X	X

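### The primary 30-day infection comparison is an unadjusted Chi2 test, although a baseline nutritional risk score is taken in every patient; adjusting for it is a modest, cost-free gain in precision

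*Protocol article*

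**What the plan says.** - **Endpoint (Clinical outcomes).** "The primary endpoint is to investigate the infectious complications rate at 30 days after surgery". The outcome is yes/no per patient.
- **Test (Statistical analysis).** "The complication rate will be compared between groups using a Chi2 test". No other between-arm test is named for a complication rate, and no covariate or stratum term is mentioned. I read the sentence as covering the primary endpoint.
- **Prognostic factor (Introduction).** "malnutrition has been identified as an independent risk factor for morbidity and mortality after cystectomy".
- **Measurement (Study design, text after Table 1).** "Nutritional Risk Status (NRS) Score will be performed in each patient before inclusion". Table 2 places it at the screening visit V0, the same visit as randomisation.
- **Allocation (Study design).** The trial uses "block randomization stratified by centers", and the text adds: "Malnutrition status will not impact the group allocation".
- **Planned use of nutritional status (Statistical analysis).** Subgroup analyses only: one of well-nourished patients, and one "to test the effect of neoadjuvant chemotherapy and the risk of malnutrition on the primary outcomes".

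**The concern.** The protocol names a prognostic factor, plans to measure it in everyone before randomisation, and then leaves it out of the primary comparison. Neither the randomisation nor the test accounts for it. The subgroup analyses do not fill the gap, because they add no precision to the overall comparison.

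Two things are at stake. The first is precision, in a trial with almost no power to spare at its design effect. The second is how a result would be defended. In a trial of a nutritional product, a visible difference between arms in nutritional risk is the first thing a critic would raise. An adjustment chosen after seeing that difference would be post hoc, and Roles and responsibilities states that the data analyst is not blinded.

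**Working it through.** **Inputs from the documents (Sample size calculations).** 37% control, 20% IN, two-sided 5%, 80% power, 110 informative patients per arm, 5% dropout, 232 enrolled.

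**Inputs assumed.** Share of patients at nutritional risk 20%, 30% or 50%; odds ratio for infection 1.5, 2, 3 or 4. The documents give neither figure.

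**1. The plan's own figure.** With mean rate 0.285:

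n = [1.96·√(2·0.285·0.715) + 0.8416·√(0.37·0.63 + 0.20·0.80)]² / 0.17² = (1.2512 + 0.5277)² / 0.0289 = 109.5, so 110 per arm.

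Power at 110 is 80.2%, and 110/0.95 gives 116 per arm, 232 in all. The plan's figure reproduces for exactly the unadjusted test that it names.

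**2. Validity.** Simulation with 10,000 trials per scenario, no treatment effect (37% in both arms), 30% at risk, odds ratios 1 to 4. Type I error was 4.9-5.1% for the Chi2 test and 4.9-5.0% for NRS-adjusted logistic regression. Both are sound.

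**3. Precision, one case in full (30% at risk, odds ratio 2).** Stratum risks that give 37% and 20% overall are 0.3205 and 0.4854 (control, not at risk and at risk), and 0.1646 and 0.2826 (IN).

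- Unadjusted variance: (0.2331 + 0.1600)/110; SE = 0.0598.
- Adjusted variance: mean within-stratum variance summed over arms, 0.3845/110, plus variance of the stratum effects, 0.00046/220; SE = 0.0591.
- Ratio of variances: 1.02, worth 220 × 0.022 ≈ 5 patients.
- Wald power Φ(0.17/SE − 1.96): 81.2% unadjusted, 82.0% adjusted. The Wald form starts about one point above the pooled-test figure of 80.2%, so only the change matters.

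**4. All assumed cases.** Ranges run over 20%, 30% and 50% at risk. The last column comes from simulation at 110 per arm, adjusted logistic minus Chi2.

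| Odds ratio | Relative efficiency | Equivalent patients of 220 | Wald power (from 81.2%) | Simulated power gain, points |
|---|---|---|---|---|
| 1.5 | 1.01 | 1-2 | 81.4-81.5% | −0.2 to +0.2 |
| 2 | 1.02 | 4-5 | 81.8-82.0% | +0.5 to +1.2 |
| 3 | 1.05-1.06 | 10-13 | 82.9-83.3% | +1.8 to +2.5 |
| 4 | 1.08-1.09 | 17-21 | 83.9-84.5% | +2.8 to +3.2 |

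At odds ratio 1 the two methods differ only by simulation error.

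**5. Chance imbalance (30% at risk).** The SD of the between-arm difference in the at-risk share is √(2·0.3·0.7/110) = 6.2 points, so a difference above 10 points has probability of about 11%. A 10-point difference moves the unadjusted risk difference by 0.10 × (0.485 − 0.321) ≈ 1.6 points at odds ratio 2, and by 0.10 × (0.599 − 0.272) ≈ 3.3 points at odds ratio 4, using control-arm risks. The unadjusted SE of 5.98 points already contains this variation. Removing it gives 5.91 points (odds ratio 2) or 5.71 points (odds ratio 4), which is the same gain as in step 4.

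**6. Model size.** Expected events: 110 × 0.37 + 110 × 0.20 = 62.7. Arm, NRS as one term, two centre indicators and optionally age make five terms, about 12 events per term.

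**The case against.** The strongest reply is that nothing here is an error. The test is valid under randomisation and agrees with its own sample size calculation, and a covariate list is often left to an analysis plan, which is not shown. The first two parts stand in full. The third stands only in part: the article does not leave the method open but names the Chi2 test. If a fuller document holds an adjusted primary analysis, the two texts need to be aligned.

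A second reply is that the gain is small and rests wholly on assumed inputs. This stands too. At an odds ratio of 1.5 the gain is nil for practical purposes. The Introduction also attributes the risk to malnutrition, not to the NRS by name, and a screening score may predict less well than the condition.

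Four stronger readings are tempting, and the documents do not support them:

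- **That the unadjusted result would be biased.** Randomisation protects it, and its type I error is nominal.
- **That chance imbalance is a further problem on top of lost precision.** It is the same loss described another way (step 5).
- **That adjusting for all screening-visit variables would bring power to 83-85%.** This needs a share of outcome variance explained that appears nowhere in the documents.
- **That oncologic versus benign indication belongs in the model as a prognostic term.** The Introduction says that the two groups have similar complication risk.

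**Conclusion.** The point holds as a free improvement, not as the correction of a mistake. The primary comparison leaves out a pre-randomisation score that is taken in every patient and that screens for a condition the protocol itself calls prognostic. The cost is modest: about 0 to 3 power points, or roughly 1 to 21 of 220 evaluable patients. That range assumes 20-50% of patients at nutritional risk, an odds ratio of 1.5 to 4 and the design rates of 37% and 20%; it shrinks to nothing if the NRS does not predict infection. The sample size needs no change. The change is still worth making, because it costs no patients and settles the handling of nutritional imbalance in advance.

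**What to change.** Before any unblinded analysis, amend Statistical analysis (and the analysis plan, if there is one) so that:

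- the primary analysis is a logistic regression of 30-day infection on arm, baseline NRS and centre, with age optional. The form of the NRS term (score or at-risk category) should be fixed in advance. Centre belongs in the model as the only stratification factor;
- the result is reported as a standardised (marginal) risk difference with a 95% confidence interval, which stays on the scale of the planned 17-point difference;
- the Chi2 test is kept as a sensitivity analysis;
- oncologic/benign indication is not added as a prognostic term, and no power above the planned 80% is claimed.

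The cost is a few lines of text and a short amendment. NRS and centre are already recorded for every patient, so no new data or patients are needed.

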### Choice of comparators and protocol adherence

Oral Impact^®^ (IN) is an immune-modulating nutritional supplement containing arginine, omega-3 polyunsaturated fatty acids, and ribonucleic acid. Arginine is a key amino acid involved in multiple cellular processes as well as in lymphocyte function and its deficiency results in impaired adaptive immune response. It plays an active role in wound healing, muscle repair (by protein translation), and thrombosis prevention. The present design raises the issue of supplementing patients that are not at nutritional risk with Oral Impact®, resulting in overnutrition with potentially deleterious clinical consequences. However, this hypothesis has not been confirmed by others [23] and the product’s brochure stipulates that the administration of Oral Impact® in the preoperative phase is also indicated in well-nourished patients [24]. Moreover, surgery induces arginine deficiency and many patients with normal preoperative arginine concentrations cannot endogenously satisfy the metabolic demand after surgery.

Patients will be randomly assigned to receive 7 days of preoperative IN, three times a day (Oral Impact^®^) or will not receive oral IN supplements. Carbohydrate loading and protein drinks will be allowed in both groups. In the interventional group, patient’s compliance to the allocated treatment will be recorded by asking the patient how many nutritional supplements she/he has ingested preoperatively (ranging from 0 to 21 bags). Compliant patients will be defined by having drunk at least 14 of the 21 allocated nutritional supplements. To objectively verify and validate these subjective data, serum arginine levels will be assessed at enrolment (between day − 30 and day − 8) and at preoperative admission after intake of the allocated nutrition (day − 1).

Potential effective crossover between intervention groups will be assessed and recorded. As usual with interventions requiring voluntary adherence to a protocol, there is a risk for some participants from the IN arm do not comply with the intervention. Moreover, a mirroring risk exists for participants from the control group to access IN independently of the study protocol, since the product is commercially available. Recording such protocol deviations is mandatory for processing to a second line per-protocol analysis. However, the risks of crossover are very low.

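### The well-nourished subgroup analysis is written for the IN arm alone, so it cannot show whether IN helps or harms well-nourished patients; the chemotherapy and malnutrition wording should be aligned with the stated aims

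*Protocol article*

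**What the plan says.** The Statistical analysis section says that nutritional status will be documented and that a "subgroup analysis of well-nourished patients randomized to the IN group will be undertaken at the end of the study". No control-arm comparator is named.

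The same section lists further subgroup analyses: first "to test the effect of neoadjuvant chemotherapy and the risk of malnutrition on the primary outcomes", then "to test the impact of the ERAS® compliance on the primary and secondary outcomes". It gives no model for either.

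Three other places bear on this:

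- **Choice of comparators and protocol adherence** acknowledges that the design raises the issue of "supplementing patients that are not at nutritional risk with Oral Impact®, resulting in overnutrition with potentially deleterious clinical consequences". It then says that others have not confirmed this and that the product brochure covers well-nourished patients too.
- **Clinical outcomes** lists among the matters to be investigated the "impact of IN on oncologic and non-oncologic patients, role of IN in patients undergoing neoadjuvant chemotherapy".
- **Study design** (text after Table 1) says that a "Nutritional Risk Status (NRS) Score will be performed in each patient before inclusion", and that malnutrition does not affect allocation. Table 2 places the score at V0, which ends on day -8, before the 7-day course of IN.

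**The concern.** Whether IN helps or harms patients who are not at nutritional risk is a question about IN versus no IN in those patients. An analysis confined to the IN arm can only describe them or compare them with malnourished patients in the same arm. The Introduction calls malnutrition an independent risk factor for morbidity and mortality after cystectomy. On that premise well-nourished patients should do better whether or not IN does anything, so a low infection rate in the one-arm subgroup would be uninformative about IN.

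At stake is a lost opportunity and a possible misreading. Well-nourished controls will be in the trial with the same baseline score, and the sentence as written leaves them out.

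The second sentence has a milder problem. The Clinical outcomes section asks what IN does in patients given neoadjuvant chemotherapy. The Statistical analysis section, read literally, asks what chemotherapy and malnutrition risk do to the outcome. The oncologic versus non-oncologic question has no counterpart in the Statistical analysis section.

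**Working it through.** **1. The plan's own figure.** Inputs from Sample size calculations: 37% versus 20%, two-sided 5%, power 80%. With pooled variance under the null and mean rate 0.285:

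n = [1.960·√(2·0.285·0.715) + 0.842·√(0.37·0.63 + 0.20·0.80)]² / 0.17² = (1.251 + 0.528)² / 0.0289 ≈ 109.5, so 110 per arm.

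This matches the stated 110. Allowing for 5% dropout, 220/0.95 = 231.6, so 232, which also matches. The article gives no figure for any subgroup.

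**2. What the one-arm analysis can identify.** Assumed rates, for illustration: 15% infections in well-nourished and 28% in malnourished IN patients.

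| Well-nourished controls (assumed) | IN minus control, well nourished | Within-IN contrast |
|---|---|---|
| 10% | 15 − 10 = +5 points (harm) | 15 − 28 = −13 points |
| 30% | 15 − 30 = −15 points (benefit) | 15 − 28 = −13 points |

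The within-arm result is the same whether IN harms or helps, so the IN effect is not identified.

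**3. What the two-arm analysis would give.** The well-nourished share s is not in the article; 40% to 80% is assumed. Per arm, n = 110·s well nourished and m = 110 − n not. Let v = 0.37·0.63 + 0.20·0.80 = 0.3931.

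- Half-width of the 95% CI for the risk difference in the well-nourished stratum: 1.96·√(v/n).
- Half-width for the interaction (difference of the two risk differences): 1.96·√(v/n + v/m).
- Power in the stratum for 37% versus 20%: the formula in step 1 solved for power.

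| Share | n, m per arm | Stratum half-width | Interaction half-width | Stratum power |
|---|---|---|---|---|
| 40% | 44, 66 | 18.5 points | 23.9 points | 42% |
| 60% | 66, 44 | 15.1 points | 23.9 points | 58% |
| 80% | 88, 22 | 13.1 points | 29.3 points | 71% |

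If IN gave a 17-point benefit in one stratum and none in the other (37% in both arms there), power for the interaction would be about 18% to 27% over these shares.

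**4. Sensitivity to the event rates.** Well-nourished patients may have fewer infections than the whole-trial rates. With the assumed rates of step 2:

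- 30% versus 15%: v = 0.21 + 0.1275 = 0.3375, half-width 17.2 points (n = 44) to 12.1 points (n = 88).
- 10% versus 15%: v = 0.09 + 0.1275 = 0.2175, half-width 13.8 to 9.7 points.

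The intervals narrow somewhat but remain wide.

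**The case against.** The strongest reply is that the article is a condensed document. Interaction terms, stratum-specific estimates and an exploratory label commonly sit in the full protocol or SAP, so their absence here is no fault. That stands. The objection to the well-nourished sentence is different: it states a population, and the population is one arm.

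A reader might infer that none of the subgroup analyses can show anything about IN, because the others test only main effects of chemotherapy and malnutrition risk. The article does not support that. It gives no model for them, calls them subgroup analyses, and does not restrict them to one arm. The Clinical outcomes section states the aim in terms of IN. An IN-versus-control comparison by nutritional risk is compatible with the plan, so what remains there is a mismatch of wording between two sections. ERAS compliance is a separate matter: it arises largely after randomization, so a comparison of arms within compliance levels would not be a clean randomized one, and it does not belong among the baseline subgroups.

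It is also fair to say that the sponsor raises overnutrition and answers it from outside sources, does not name this subgroup as the test of it, and attaches no decision to the result. A reader might infer that a low one-arm rate will be reported as evidence of safety; nothing in the article says so. This lowers the weight of the point. It does not give the one-arm analysis a comparator.

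**Conclusion.** The point holds for the well-nourished analysis. Followed as written, it yields no estimate of the effect of IN and cannot inform the overnutrition issue. The wording on neoadjuvant chemotherapy and malnutrition risk is a secondary mismatch with the stated aims.

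The weight is moderate to minor. Only exploratory analyses are affected, and the primary intention-to-treat comparison and its sample size stand. The corrected analysis would itself be imprecise: about 13 to 18.5 points either side in the well-nourished stratum and 24 to 29 points for the interaction. Those figures rest on an assumed well-nourished share of 40% to 80%, on 110 evaluable patients per arm, and on the whole-trial rates of 37% and 20% in each stratum. The conclusion about the missing comparator rests on none of these assumptions.

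**What to change.** Replace the one-arm sentence with wording such as:

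> *The risk difference (IN minus control) in infectious complications at 30 days, with its 95% CI, will be estimated separately in patients at and not at nutritional risk by NRS at V0, with a treatment-by-NRS interaction term. This analysis is exploratory.*

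Reword the sentence on neoadjuvant chemotherapy and malnutrition risk so that it asks for the effect of IN versus control by baseline neoadjuvant chemotherapy status, malnutrition risk and indication (oncologic or non-oncologic), in line with the Clinical outcomes section. If the full protocol or SAP already says this, only the article's sentences need correcting.

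The cost is wording. NRS is already scored in every patient before inclusion. Chemotherapy history and indication should be available from the medical history that Table 2 schedules at V0, although the article does not itemize them. No extra patients or visits are needed. The change should be made before outcome data are analysed by arm, the more so because the article says that the data analyst is not blinded.
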